#### Sample size estimate / power calculations

The required sample size was calculated with G*Power (Version 3.1.9.2, Heinrich Heine University of Duesseldorf) [62]. The sample size calculation was approximated with a 2 × 3-factorial analysis of variance (ANOVA) for repeated measures (within-between interaction, small effect size, power of .80 [1-β], 2-sided α-error (95% CI), 2 groups, 3 measurements) based on the primary outcome Short Physical Performance Battery (SPPB). The small effect size used for the calculation of required sample size is based on literature reviews and assumptions of clinically relevant changes for residents in nursing homes with probable cognitive impairment [63]. One hundred eight individuals per region are required in order to detect a clinically meaningful change of ≥1.0 point with a SD of 0.99 points. To account for potential dropouts before study completion, we will inflate the sample size by 30% (20% losses during follow-up; 10% mortality), resulting in a total sample size of 1120 individuals (140 per centre with 70 participants allocated to each group).

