##### Physical functioning

The *Short Physical Performance Battery* (SPPB) [45] is a standardized instrument to test the lower extremity functionality (balance, gait speed, leg strength). Participants are required to show a stable stand in an upright position under three conditions (legs closed/feet together, semi-tandem stand, tandem stand). After that, comfortable gait speed will be assessed by measuring the time to walk a 4-m track, starting from a standing position and stopping when the first foot is past the 4-m line. Finally, a five times sit-to-stand transfer will be completed as fast as possible. Each domain is scored between 0 and 4 and SPPB overall scores range from 0 (low mobility/functionality) to 12 (full mobility/functionality). Clinically relevant improvements have been demonstrated to range between 0.99 and 1.34 points for the SPPB [45].

*Gait analysis* (GAITRite: CIR Systems Inc., Clifton, NJ, USA, Optogait: Microgate, Bolzano, Italy, MobilityLab: APDM Inc., Portland, USA, GaitUp: SA, Lausanne, Switzerland or Zebris PDM, Isny, Germany). Gait performance will be assessed by measuring step length, step width, gait speed, and double support phase on a 10-m track, using of one of the mentioned gait analysis systems. Each participant completes three trials: a test trial, one trial at preferred walking speed, and one trial at maximum walking speed. Measured data will be recorded and saved for later analysis by the gait systems software. An accompanying validation study will secure the comparability of the different gait measurement systems.

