### Data collection, management, and analysis

#### Statistical analysis

We will evaluate the effects of the intervention on every quantitative, qualitative, and ordinal outcome, using repeated measures or mixed models, “t” tests, Kruskall-Wallis Mann-Witney tests or the Chi-square tests, depending on the type of outcome and their normal or non-normal distribution. The primary analysis will be a mixed model between-group comparison of the SPPB, gait variables, Serial Sevens, and Verbal Fluency Test, utilising all available data points during follow-up. We will use the Bonferroni correction to appropriately adjust the overall level of significance for multiple comparisons. Between-group differences for all primary and secondary outcomes will be adjusted for baseline values, age, sex, and education. Secondary outcomes will be analysed with similar methodology, using repeated measures mixed model between-group comparisons. All statistical analyses will be performed using SPSS Statistics for Windows (version 25.0, IBM). Statistical significance level is set at *p* < 0.05.

Intention-to-treat analysis will be performed (participants who are randomized into groups after the collection of baseline data). For the intention-to-treat analysis, data of all trial patients in the groups to which they were randomized will be processed, regardless of whether they received or adhered to the allocated intervention. It is assumed that the majority of participants in the two arms will receive the appropriate number of intervention sessions. In addition, a per-protocol analysis of the participants who completed the study without major protocol violation (e.g., who attended more than 80% of the training sessions), will be performed. The per-protocol analysis will be performed as a secondary analysis, if there is a sufficient number of participants in the two arms, who do not receive the intervention protocol or are lost to outcome assessment. Data from those participants, who do not violate the treatment protocols, will be included in the per-protocol analysis. The multiple imputation (MI) technique will be used for dealing with missing data under the assumption that data are missing at random.

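### The sample-size paragraph attaches two disagreeing effect sizes to 108 per region, and its 80% power is stated for one region although one overall comparison is planned

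*Protocol article*

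**What the plan says.** All of the following is in the protocol article.

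- **Sample size estimate / power calculations**, method: "The sample size calculation was approximated with a 2 × 3-factorial analysis of variance (ANOVA) for repeated measures". The settings listed are "within-between interaction, small effect size, power of .80 [1-β], 2-sided α-error (95% CI), 2 groups, 3 measurements", applied to the Short Physical Performance Battery (SPPB). On the effect: "The small effect size used for the calculation of required sample size is based on literature reviews". No numerical f and no correlation between repeated measures is given.
- **Same section**, result: "One hundred eight individuals per region are required", and the purpose given for that number is "to detect a clinically meaningful change of ≥1.0 point with a SD of 0.99 points". The 108 is then raised for losses ("we will inflate the sample size by 30% (20% losses during follow-up; 10% mortality") to 140 per centre, which over eight centres makes 1120.
- **Statistical analysis**: the primary analysis is one mixed-model comparison between the two groups, for SPPB and several other outcomes, with a Bonferroni correction and a 5% significance level. No region-specific analysis is described.
- **Primary outcomes, Physical functioning**: "Clinically relevant improvements have been demonstrated to range between 0.99 and 1.34 points for the SPPB".

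**The concern.** One sample size is justified by two effect descriptions. Conventionally, a small effect is a fraction of a standard deviation. One point with SD 0.99 is a whole standard deviation. If 108 follows from the first, the claim made with the second is wrong.

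The 80% power and the 1.0-point target are also tied to a single region of 108, while the inference will apparently come from eight regions together. A reader therefore cannot learn from the article which SPPB difference the trial as a whole was built to detect. This is the article's only justification for recruiting 1120 nursing home residents and its only power statement for a primary outcome.

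**Working it through.** **Inputs.** From the documents: 2 groups, 3 measurements, within-between interaction, power 0.80, two-sided alpha 0.05, 108 per region, eight regions, difference 1.0, SD 0.99. Assumed, because not given: small means f = 0.10; correlation rho between measurements ranges from 0 to 0.8; sphericity holds. I take the 2 × 3 layout as stated.

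**Formula.** For total N, k = 2 groups and m = 3 times, power comes from a noncentral F with λ = f²·N·m/(1 − rho), df1 = (k − 1)(m − 1) = 2 and df2 = (N − k)(m − 1).

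**Step 1: reproduce 108 from the small effect.** With f = 0.10:

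| rho | N for 80% power | power at N = 108 |
|---|---|---|
| 0 | 324 | 34% |
| 0.3 | 228 | 47% |
| 0.5 | 164 | 61% |
| 0.6 | 130 | 72% |
| 0.67 | 108 | 80% |
| 0.7 | 98 | 84% |
| 0.8 | 66 | 96% |

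At rho 0.67, λ = 0.01 × 108 × 3/0.33 = 9.8. The 108 is reproduced there; at rho 0.5 it would need f of about 0.123 instead.

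**Step 2: put 1.0 point with SD 0.99 into the same design.** The standardised difference is 1.0/0.99 = 1.01. The interaction f depends on how the group difference develops over T1, T2 and T3:

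- Full difference at T2 and T3 (0, 1, 1): the mean difference is 2/3, so the interaction terms are half the deviations: −1/3, 1/6, 1/6. Their mean square is 1/18 and the root is 0.2357. f = 0.2357/0.99 = 0.238.
- Linear growth to T3 (0, 0.5, 1): the terms are −0.25, 0, 0.25. Their mean square is 0.0417 and the root is 0.204. f = 0.204/0.99 = 0.206.

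| rho | N, f = 0.238 | N, f = 0.206 |
|---|---|---|
| 0 | 60 | 78 |
| 0.3 | 42 | 56 |
| 0.5 | 30 | 40 |
| 0.67 | 22 | 28 |

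The requirement is 22 to 78 per region. At N = 108 the power is at least 92% (f = 0.206, rho 0) and above 99.8% at rho 0.5. A plain two-sample t test of 1.0 with SD 0.99 needs 17 per arm (34 in all), and 54 per arm gives 99.9% power.

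**Step 3: translate the small effect back into points.** With SD 0.99, f = 0.10 is 0.10 × 0.99/0.2357 = 0.42 points for the flat pattern, or 0.10 × 0.99/0.204 = 0.49 points at T3 for the linear one. For one point to equal f = 0.10, the SD would have to be 0.2357/0.10 = 2.4 (flat) or 0.204/0.10 = 2.0 (linear).

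**Step 4: one region against all regions.** The planned number before losses is 8 × 108 = 864. After 30% loss from 1120, 1120 × 0.7 = 784 remain, or 392 per arm. For f = 0.10, power with 784 is 99.4% at rho 0 and higher at larger rho, before Bonferroni or clustering.

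The detectable difference in a simple two-group comparison with 392 per arm is (1.96 + 0.84) × √(2/392) = 0.20 SD. The article does not give the number of Bonferroni tests or a clustering allowance. Assuming 4 to 12 tests, 1.96 becomes 2.50 to 2.87, giving 0.24 to 0.27 SD (rounding up from 0.265). With an assumed variance inflation of 1.2, multiplying by √1.2 gives 0.26 to 0.29 SD. Baseline adjustment would lower these values.

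In points, 0.24 to 0.29 SD is 0.24 to 0.29 if the SD is 0.99, and about 0.6 to 0.9 if the SD is 2.5 to 3 (an assumed range).

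**The case against.** **The two inputs might still meet.** The article never puts a number on small, and the software offers another effect-size convention (as in SPSS) under which f of about 0.215 gives N = 108. That f lies within the 0.206 to 0.238 range for 1.0/0.99. A reader might infer that the inputs can never both yield 108; that is too strong. But it takes that convention and a particular time pattern, neither of which the article mentions, and 0.215 is more than twice the usual small value.

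**The 108 may be sound.** A condensed article may leave the correlation to the full protocol, and f = 0.10 at rho 0.67 gives 108. This stands: the omitted correlation is no fault in itself. What fails is the printed statement about what 108 per region can detect.

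**Powering each region is cautious.** That is a legitimate choice, and the article never uses the word pooled. An analysis across regions is inferred from the single between-group model and the single total. Even so, the printed power and detectable difference then do not describe the comparison that will be reported.

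**The 0.99 looks like a relevance bound used as an SD.** It equals the lower end of the range in the outcome section. A reader might infer a transcription error, but the match alone does not show it, and the cited sources are not available here.

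**Trivial differences will be significant.** A reader might infer this from the pooled numbers. The documents do not support it: a detectable difference at 80% power is not a guarantee of significance, and with Bonferroni, clustering and a larger SD it could approach 0.99 points.

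**Conclusion.** The paragraph is wrong as written under ordinary settings. If small means f = 0.10, 108 per region fits only a correlation near 0.67, and with SD 0.99 the matching difference is about 0.4 points rather than 1.0. If 1.0 point with SD 0.99 is meant, 22 to 78 per region suffice for correlations from 0.67 to 0, and 108 has far more than 80% power. The two inputs differ by a factor of about 2.1 to 2.4 in f.

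Separately, the 80% power and 1.0-point target belong to one region and do not carry over to the apparent across-region comparison.

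This rests on f = 0.10 for small, on reading 0.99 as the outcome SD, on the stated 2 × 3 layout with sphericity, and on inferring that the mixed model covers all regions. It does not show that 1120 is too few, nor that the SD was mistaken. The trial may well detect SPPB differences below 0.99 points, so statistical significance alone would not establish relevance.

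**What to change.** Keep 1120. In the sample-size section:

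1. Delete or correct the statement that 108 per region detect one point with SD 0.99.
2. Restate power for the planned mixed-model comparison across regions, using one effect size expressed both as f and in SPPB points.
3. Give an SPPB SD with its source, after checking where 0.99 came from, and the assumed correlation between measurements.
4. Use the Bonferroni-adjusted alpha that the analysis section implies, and make an allowance for clustering.
5. State the resulting detectable difference in points.

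In the analysis section, add that the SPPB estimate and its confidence interval will be interpreted against the protocol's own 0.99–1.34 range.

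The cost is a short recalculation and a rewritten paragraph. Recruitment, allocation and the planned tests do not change; only the stated power and detectable difference do.

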#### Monitoring

A data monitoring committee, responsible for data monitoring, interim analyses and auditing, will not be established, because no adverse events are to be expected. However, study participants will be under the surveillance of trained project staff, who will intervene, if a negative reaction is observed during the measurements and training interventions. Nevertheless, grant holders are part of a PROCARE advisory board and responsible for data audits every 5 months.

#### Dissemination

The results of the study will be published in open-access and international journals. In addition, the results will be presented at conferences as well as in the participating nursing homes.

## Discussion

To determine the efficacy and feasibility of a multicomponent exercise intervention for nursing home residents, a multicenter intervention study will be conducted. We assume improvements or a slower decline of frail and pre-frail residents’ physical and cognitive functioning as well as psychosocial well-being compared to a waiting time control group.

Preventive physical activity interventions could preserve the health-related quality of life of nursing home residents, since a reduction is based particularly on a loss of physical functioning [41]. We propose, that nursing home residents with severe physical and cognitive impairment might benefit from participation in physical activity interventions, because of their low functional status at the beginning and a higher physiological adaptation to a progressive training intensity [41].

There are only vague guidelines for the content, intensity, frequency, and duration of physical activity in the nursing home setting [40], yet. High-quality studies are required to close this gap and provide effective and efficient exercise modalities for this setting. The results of the present study will yield recommendations for exercise interventions, which then can be implemented into the health care system.

The intervention of this study program combines components of exercise programs that have proven to gain health benefits for residents in nursing homes [1, 12, 16] in residential care [7, 56], and in older adults living in the community [20, 35, 57–59], with a special focus on cognitive-motor exercises. Furthermore, based on this multicomponent program with strength, balance, and dual-task components, the findings will help to derive valid recommendations for activities and guidelines for health promotion in nursing home residents. Results from this trial will particularly contribute to the evidence on cognitive-motor approaches in the maintenance of mental and physical functioning. It will also offer potential ways to encourage nursing home residents to participate actively in social life within the care setting, by providing a program that is appropriate and adapted to residents’ capacities, needs and desires. To this end, the findings may provide suggestions and support to deal with present and future challenges, occurring at health promotion initiatives in the setting of nursing homes, a sector that likely will gain more relevance in times of the demographic change. With the Prevention Act of 2015, German health insurances have to provide preventive services in nursing homes [5]. The trial will show that universal prevention through physical activity interventions in this setting in late life care is possible and useful to improve health status and personal resources of nursing home residents.

## Data Availability

Data can be obtained from the corresponding author upon reasonable request.

## Abbreviations

ADL: Activities of daily living
BMI: Body Mass Index
CES-D: Center for Epidemiological Studies Depression Scale
FES-I: Falls Efficacy Scale international
GCP: Good Clinical Practice
GDS: Geriatric Depression Scale
MoCa: Montreal Cognitive Assessment
PROCARE: Prevention and occupational health in long term care
S1T: Serial 1 Test
S3T: Serial 3 Test
SD: Standard deviation
SF 12: Short Form (12 questionnaire) SF 36 Health Survey
SPPB: Short Physical Performance Battery
SST: Serial Sevens Test
SWLS: Satisfaction with Life Scale
TWT: Trail Walking Test
VFT: Verbal Fluency Test
